## ***C. Feasibility***

The feasibility of the intervention and research is based on a preliminary study on six patients which resulted in a psychiatry thesis (71) and showed the importance for the users of having a facilitator-peer-worker present in the drafting of the document and of sharing it with the psychiatrist. It also led to the appropriation of the document by a users' organization, Eutopia, who perfected the document for a better acceptability of filling it in. Integrating the mastery of this document in the program of a recovery training center, Centre de Formation au Rétablissement (CoFoR-Marseille), since September 2017 helps homogeneous diffusion of this practice to peer-workers who will be in charge of assisting patients to fill out the document. Finally, the proximity of the research actors with the field actors, through professional affiliation, previous and ongoing partnerships is a guarantee for the feasibility of the trial, in all its articulated sections.

## ***D. Limitation and justification***

### **1. Experimental plan**

The experimental plan retained is based on a randomized experimental diagram. In the light

of discussions about the generalization of the approach it is important to propose the trial diagram that brings the highest level of formal proof and the most recognized.

This plan's limit is linked to the potential contamination of the control group. The knowledge of this potential bias could have justified a cluster study or a Zelen design (96). The fact that the patients were randomly drawn by the investigators avoided this bias but introduced a new major limit which is the extreme diversity of investigator practices concerning involuntary hospital admission (professional practices linked to the place of work or the specialization), thus the need to greatly increase the number of subjects in the trial. Zelen design is a methodology that has never been used in France, and which presents the particularity of only informing the person which experimental arm they are in. Using this technique, which would reduce access to advance directives for the control group, from an ethical point of view this presents the particularity of privileging the principle of benevolence (limiting the feeling of "missing a chance") over the principle of autonomy (being informed of the entire research project). Given the central importance of the notion of autonomy in this research, classical randomization was chosen.

## **2. Contagion of controls**

The risk seems limited by the limited current knowledge about this approach. Publicity will be limited by the sample size in each city (50 people will fill in the document), the large number of psychiatrists involved (2 to 4 per site), ambulatory inclusion (versus hospital inclusion, where patients talk a great deal among themselves), and the narrow window of inclusion (6 months).

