## ***C. Number of subjects necessary and feasibility***

### **1. Number of subjects necessary**

Subjects included in the trial are people who were involuntarily admitted to hospital within the previous 12 months. According to data in French literature, the rate of involuntary hospital admission for patients suffering from psychotic disorders is 42.6% within 12 months after their previous admission(27).

Reducing these involuntary admissions by one third, i.e. 33%, would be a very significant reduction in terms of efficiency. This is a realistic hypothesis in the light of the most recent meta-analyses (59). We consider that 10% of participants will not reach experimental intervention and we estimate a 30% size effect. With these hypotheses, for an alpha risk of 2.5% (one-sided test) and 80% power, 182 subjects per group would be necessary. Over a 12-month period rate of lost to follow-up equal to 10% has been considered acceptable by the investigators involved in this project, especially with regards to the means scheduled to limit the number of people lost from sight.

Accordingly, the total number of subjects to include is 400 patients.

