### **2. Feasibility – Trial duration**

#### **2.1. Scaling up**

Inclusions will be progressive as the patients present inclusion criteria (open trial), and as the peer-worker and interviewer are able to meet new people.

Recruitment of patients will be progressive, until reaching 150 people per site for the Lyon and Marseille sites, 100 people for the Paris site, over an estimated period of 12 months. For each subject the duration of follow-up is fixed at 12 months. In total, this trial will have a duration of 30 months including 6 months of analysis.

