## 2. Risks and constraints

On an individual level, the risks for patients who are “beneficiaries of usual care” of participating in the trial are low. There can be a feeling of losing a chance when they are told they are in the control group, double-blinding being impossible. However there is no change in their usual care pathway, and the patients will not be prevented from drafting advance directives if they take their own initiative to do so. The constraints are related to the fact that they have to go to meetings scheduled with the interviewer.

The individual risks and constraints of the patients who are “beneficiaries of the experimental program” are related to the introspection necessary for the drafting, which can cause a painful evocation of the past, related to previous episodes of coercion; there is also the meeting with the peer-worker, who is an atypical professional, which could destabilize some patients depending on the representations and potential expectations that they may have concerning this meeting.

Another constraint is related to answering the survey questionnaires according to a calendar defined in advance with the interviewer.

On an individual level, a risk related to the use of psychiatric nosology at the time of inclusion for both groups of patients, the use of the stated illnesses can be painful for certain patients who are in denial of their disorders. This is a lesser risk in the experimental arm because of the presence of the peer-worker, who has an impact on destigmatization.

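### The contamination argument uses recruitment figures the plan contradicts, directives in controls are not explicitly recorded, and 182 per group gives about 72% power at the stated 30% effect

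*Combined protocol and SAP*

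**What the plan says.** **Contamination.** VIII.D.1 (Experimental plan) names contamination of the control group as the limit of the design. It says that this could have justified a cluster or Zelen design, and keeps individual randomization for other reasons. VIII.D.2 (Contagion of controls) then gives five reasons why the risk appears limited: the approach is little known, few people per city will have a directive, 2 to 4 psychiatrists per site are involved, inclusion is ambulatory, and recruitment is short. Two of these carry figures: "Publicity will be limited by the sample size in each city (50 people will fill in the document" and "and the narrow window of inclusion (6 months" (both within parentheses in the source).

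**Recruitment.** VI.C.2.1 (Scaling up) plans "150 people per site for the Lyon and Marseille sites, 100 people for the Paris site, over an estimated period of 12 months". The Calendar (VII) starts inclusions at M0 and ends them at M12.

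**Exposure of controls.** Under VI.B.1 (Detection – Eligibility) the psychiatrist explains the intervention to every candidate before randomization. IX.A.2 says of usual-care patients that "the patients will not be prevented from drafting advance directives if they take their own initiative to do so".

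**Measurement.** VI.A.2.2.b lists the number of directives completed among the process indicators. VI.A.3 schedules those indicators at baseline, 6 and 12 months for both groups. No item is worded for directives written by controls.

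**Sample size.** VI.C.1 takes a control rate from the literature: "the rate of involuntary hospital admission for patients suffering from psychotic disorders is 42.6% within 12 months after their previous admission". The target reduction is one third (33%), and then: "We consider that 10% of participants will not reach experimental intervention and we estimate a 30% size effect". The result is: "for an alpha risk of 2.5% (one-sided test) and 80% power, 182 subjects per group would be necessary". With 10% loss to follow-up the total is 400. There is no term for directives in controls.

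**The concern.** VIII.D.2 is the protocol's only argument that its self-declared main limit is small, and two of its figures do not describe the trial in the recruitment plan. The longer the window and the more directive-holders per city, the more chance that a control, or a psychiatrist treating both arms, carries the idea across.

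Contamination pulls the difference towards zero. If nobody records how many controls wrote a directive or crisis plan, a null result cannot be separated into no effect and a diluted contrast. The record could not be rebuilt later from the documents themselves, since the title of Annex 5 says that they are not collected for analysis. The SAP's per-protocol definition (completing the intervention originally allocated) does not say how a control with a directive would be handled.

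The margin for absorbing any dilution depends on the sample size, so it matters whether 182 per group delivers 80% power under the effect that the section states.

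**Working it through.** **1. Recruitment figures side by side.**

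| Item | VIII.D.2 | VI.C.2.1 and Calendar |
|---|---|---|
| Inclusion window | 6 months | 12 months (M0 to M12) |
| Directive-arm patients per city | 50 | 150/2 = 75, 150/2 = 75, 100/2 = 50 |

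The halving assumes 1:1 allocation, which the 182 per group implies but the protocol does not state. The 12-month figure agrees with the rest of the plan. At the rates in VI.C.2.2 (Recruitment), 12.5 × 12 = 150 and 8.5 × 12 = 102 patients, whereas 6 months would give (12.5 + 12.5 + 8.5) × 6 = 201 of the 400. The stated 30-month duration is also 12 + 12 + 6.

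**2. Reproducing 182 per group.** Inputs from VI.C.1: control rate p1 = 0.426, one-sided alpha 2.5% (z = 1.960), power 80% (z = 0.8416). Pooled-variance normal approximation:

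n = [1.960·√(2p̄(1−p̄)) + 0.8416·√(p1(1−p1) + p2(1−p2))]² / (p1−p2)²

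- 33% reduction: p2 = 0.426 × 0.67 = 0.2854. n = (1.960 × 0.6770 + 0.8416 × 0.6697)² / 0.1406² = 180.9, so 181. This matches 182. An exact one third gives 178.
- 30% reduction: p2 = 0.426 × 0.70 = 0.2982. n = (1.960 × 0.6797 + 0.8416 × 0.6736)² / 0.1278² = 220.8, so 221. This does not match. Other methods are no closer: 219 unpooled, 237 with continuity correction, and 174 at one-sided 5%.

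One third × 0.9 = 30%, so the 30% is the target after 10% non-reach. The printed 182 therefore belongs to the effect before that dilution. The total follows from it: 2 × 182 × 1.1 = 400.4.

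**3. Power at 182 per group, no contamination.**

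Power = Φ{[(p1−p2)√n − 1.960·√(2p̄(1−p̄))] / √(p1(1−p1) + p2(1−p2))}

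- 33%: (0.1406 × 13.49 − 1.327) / 0.6697 = 0.85, so 80.2%.
- 30%: (0.1278 × 13.49 − 1.332) / 0.6736 = 0.58, so 72.0%.

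**4. Sensitivity to contamination.** Let a share c of controls obtain the full effect RRR. The control rate becomes 0.426 × (1 − c × RRR). Both c and the full effect are assumptions. The 3% row borrows the only related figure in the documents, the share who write a directive without a facilitator (I.E.1.1). Applying it to these controls is also an assumption.

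| c | Control rate (33% / 30%) | Power at 182, 33% effect | Power at 182, 30% effect | n per group for 80% (33% / 30%) |
|---|---|---|---|---|
| 0% | 0.4260 / 0.4260 | 80.2% | 72.0% | 181 / 221 |
| 3% | 0.4218 / 0.4222 | 77.9% | 69.4% | 192 / 235 |
| 5% | 0.4190 / 0.4196 | 76.2% | 67.7% | 200 / 244 |
| 10% | 0.4119 / 0.4132 | 71.8% | 63.1% | 222 / 271 |

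If contaminated controls receive only half the effect, power at 5% and 10% is 78.3% and 76.2% (33% effect), or 69.8% and 67.7% (30% effect).

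**The case against.** The protocol does not claim that contamination is negligible. It calls it the design's limit and says only that the risk appears limited. Two of its reasons, limited current knowledge of the approach and ambulatory inclusion, do not depend on the disputed figures, so asking for the conclusion to be withdrawn would go too far. This stands: the conclusion needs re-justifying.

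A reader might infer that 50 per city comes from a smaller trial. The documents do not show that. The qualitative section still describes four sites, and 4 × 50 = 200 is the same directive-arm total as 400/2. The figure also fits Paris as planned, and it could mean people who complete the document rather than people allocated. It is low for two cities only.

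A reader might also divide 150 patients by 2 to 4 psychiatrists and conclude that each treats about 38 to 75 trial patients. That is unsafe: versions V3 and V4 added hospitals, and it is unclear whether 2 to 4 applies per city or per hospital.

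Measurement is partly planned, since process indicators cover both arms. What is missing is explicit wording for controls.

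Finally, hearing about the intervention is not receiving it. Under IV.A.1 only the experimental arm is offered the document and the peer-worker, and contamination cannot create a false benefit. That is fair, and it is why the contamination levels above are sensitivity values and not predictions.

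**Conclusion.** Three things hold. First, the 6-month window contradicts the 12-month plan, and 50 per city is too low for Lyon and Marseille if allocation is 1:1. Second, directives written by controls are allowed but not explicitly recorded. Third, 182 per group gives 80% power only for the undiluted 33% reduction; at the stated 30% effect power is about 72%, and 221 per group would be needed.

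The tempting stronger reading is that contamination by itself proves the 80% overstated. The documents do not support it, because they give no contamination rate. At an assumed 3% with full effect the loss is about 2.5 points; at 10% it is about 8 to 9 points. The fall from 80% to 72% has a different cause, the omitted 10% non-reach, and should not be attributed to contamination. All power figures rest on a 42.6% control rate, 1:1 allocation, 182 evaluable patients per group and the normal approximation.

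**What to change.** - **VIII.D.2:** reconcile the inclusion window and the number of directive-holders per city with VI.C.2.1 and the Calendar. Give the actual number of psychiatrists after the V3 and V4 sites opened. Then re-justify the conclusion, stating which reasons still carry it.
- **VI.A.2.2.b and VI.A.3:** add to the existing process indicators at months 6 and 12 one question to each control patient and one to the psychiatrist, asking whether an advance directive or crisis plan was written. Report that proportion beside the primary result.
- **VI.C.1:** state that 182 per group corresponds to the undiluted 33% reduction, and give the power at the 30% effect (about 72%). Show power for assumed contamination of 0%, 5% and 10%: about 72%, 68% and 63% at 30%, and 80%, 76% and 72% at 33%.

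The cost is text changes, two eCRF items at visits already planned, and a less favourable stated power. No extra patients are required by these changes.

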## **3. Absence of pairing**

The implemented project does not offer pairing upon inclusion thus limiting comparability. The choice not to pair was based on the following observations:

- the factors of confusion to be taken into account have not yet been clearly defined;
- pairing according to variables such as age and gender would weigh down the procedure and limit inclusion;
- from an ethical point of view it seems difficult to propose pairing which requires prior randomization and which could lead to non inclusion in the project even though the population was solicited

The principle of prioritizing reality on the field, and the supposed or identified factors of confusion will be taken into account upon analysis as described in chapter VII. D. 3.

# **IX. Ethical and regulatory aspects**

## **A. Risk-benefit ratio**

### **1. Benefits and advantages**

Benefits are on a community and an individual level. On a community level, this research will provide elements of reflection for public authorities concerned with caring for homeless people with mental disorders, in order to improve the health, the care pathway, the autonomy and the respect of the rights of this vulnerable population while managing to control expense.

On an individual level, patients included in the study benefit from a reimbursement of their

travel expenses resulting from their coming to the center for the visits, upon presentation of proof.

Since the interviews required for research are led by people trained to listen and support, the patient will be able to express him/herself on these occasions.

The beneficiaries of the experimental program will have access to an innovative approach, will be able to meet a peer-worker if they wish, which generally causes about a positive identification; they will be able to share information with their psychiatrist for less coercive future treatment.

The patients benefiting from usual care will benefit from regular meetings with the person leading research.

## 2. Risks and constraints

On an individual level, the risks for patients who are “beneficiaries of usual care” of participating in the trial are low. There can be a feeling of losing a chance when they are told they are in the control group, double-blinding being impossible. However there is no change in their usual care pathway, and the patients will not be prevented from drafting advance directives if they take their own initiative to do so. The constraints are related to the fact that they have to go to meetings scheduled with the interviewer.

The individual risks and constraints of the patients who are “beneficiaries of the experimental program” are related to the introspection necessary for the drafting, which can cause a painful evocation of the past, related to previous episodes of coercion; there is also the meeting with the peer-worker, who is an atypical professional, which could destabilize some patients depending on the representations and potential expectations that they may have concerning this meeting.

Another constraint is related to answering the survey questionnaires according to a calendar defined in advance with the interviewer.

On an individual level, a risk related to the use of psychiatric nosology at the time of inclusion for both groups of patients, the use of the stated illnesses can be painful for certain patients who are in denial of their disorders. This is a lesser risk in the experimental arm because of the presence of the peer-worker, who has an impact on destigmatization.

## 3. Risk-benefit ratio

Overall, the risk-benefit ratio corresponding to participating in this trial can be considered favorable.

### *B. Legal and ethical aspects*

The **sponsor** for this project is represented by the **Assistance Publique des Hôpitaux de Marseille**. A regulatory watch will be carried out by the Sponsor. It will submit the project to the authorities for approval.

## 1. Institutional review board

This project is in the framework of **interventional research (category 2)** with minimal risks and constraints, according to terms in article L.1121-1 paragraph 2.

It is subject to a new regulatory measure which applies to research "involving human subjects" i.e. act n° 2012-300 of March 5, 2012 relating to research involving human subjects (called the Jardé act) as amended by Order n° 2016-800 of June 16, 2016, and its application decrees.

It is for this reason that it required the opinion of a **Comité de Protection des Personnes (Ethics committee)**.

**People under (reinforced) curatorship** are purposely kept within the scope of the trial, for representativeness, and considering the importance of the benefit expected for these patients this justifies the predictable risk incurred, which is minimal, as are the constraints related to this research.

Indeed, the Code de Santé Publique (French public health regulations) states in article L. 1121-8 that adult persons under a measure of legal protection or incapable of expressing their consent may only be included for category 2 research if research of comparable efficiency cannot be carried out on another category of the population and with the following conditions: (1) either the importance of the expected benefit for these persons is such that it justifies the predictable risk incurred; (2) or this research is justified with regards to the expected benefit for other people in the same situation. In this case the predictable risks and the constraint of this research must be of minimal extent.

An **information sheet** will be handed to patients and **informed consent** will be collected from the person, information will also be given to the legal representative if the person is under curatorship. Information sheets and informed consent forms were drawn up in compliance with regulatory recommendations, stating namely the objective of the trial, the benefits and risks related to this trial, the trial procedure and all of the legal provisions to which the patients are entitled.

This research will be led according to good clinical practice, representing a group of quality requirements in the fields of ethics and science, which must be met during the planning, implementation, leading, monitoring, quality control, audit, data collection, analysis and expression of results. Respecting these good clinical practices guarantees the protection of rights, security and the protection of the people participating in this research and the preservation of their anonymity as well as the credibility and accuracy of the data and results of this research.

## 2. Data protection

Data collected during the trial will be computer processed according to the loi "Informatique et Libertés" (French data protection act) n°78-17 of January 6, 1978 (article 40), these data will only be transmitted to the sponsor and if appropriate to authorized health authorities, under conditions guaranteeing their confidentiality.

Concerning the computer processing of data relating to this project, which has the purpose of research in the field of health, it falls within the framework of legal requirements, particularly the act of August 9, 2004 and will only concern data that does not allow the direct or indirect identification of the people concerned. It will be carried out in compliance with reference methodology accredited by the Commission nationale de l'informatique et des libertés and established in concertation with the consultative committee for the processing of data in matters of research in the field of health, set up in order to simplify formalities (Deliberation n°2016-262 of July 21, 2016 on the modification of the reference methodology

for the processing of personal data operating in the framework of biomedical research. Reference methodology MR-001).

It will also be carried out in compliance with the General Data Protection Regulation (GDPR) n° 2016/679 in force on May 25, 2018. This data processing reposes on the execution of a mission of public interest for which the data controller is responsible (article 6.1.e of GDPR), in the field of public health for scientific research purposes (paragraphs i and j of article 9.2 of GDPR).

In compliance with legal requirements of the French data protection act (Act n°78-17 of January 6, 1978 amended by act n° 2004-801 of August 6, 2004), and article 13 of the GDPR n°2016/679 in force on May 25, 2018, the patient has a right to access, rectify and erase collected personal data as well as a right to limit and to object to the processing of their data. He/she also has the right to object to the transmission of this data, under the obligation of professional secrecy, susceptible of being used in the frame of this research and of being processed.

Medical and non-medical staff involved in this research are sworn to medical and professional secrecy with regards to patient data collected during the trial. Collected patient data remains strictly confidential. It will be kept in paper form in a locked premises. It will be entered on a computer and benefit from automatic processing. This computer processing will not permit direct or indirect identification of subjects. All of the data may only be consulted by the principal investigator and the Sponsor's representatives, or be transmitted to the Approved Health Authorities if necessary. Subjects can access their computer file by applying to a physician at the center.

